## Objectives

### Main objective

The main objective is to undertake a randomized clinical trial to evaluate the effectiveness of a group cognitive-behavioral transdiagnostic intervention (PsicAP) compared to the typical PHC treatment for ED patients in the Dominican Republic at 3 months, and to explore if results are maintained over time (6 months). The main outcomes will include decreased symptoms of anxiety, depression and somatization, as well as remission of potential cases of ED.

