### Study design

This is a randomized, controlled, two-armed clinical trial, with one arm consisting of the control group that will receive usual PHC treatment and another consisting of the experimental group receiving treatment according to PsicAP protocol. It should also be clarified that this is a simple blind trial, specifically in the fact that the evaluators are not the same psychologists as those giving the treatment. However, the study will not be blind in some respects, as patients can guess which group they belong to (since it is not possible to blind this condition), as will the therapists. Study participants will be assessed at 6 and 12 months after the seventh study session.

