## Interventions

### Control group treatment

The control group will receive the TAU provided by the primary care physician at the PC center. This treatment has been described in previous research as no treatment, standard treatment, pharmacological treatment and/or practical advice by the GP provided in routine care (Watts et al., 2015). In the Dominican Republic, as in other countries such as Spain (Cano-Vindel et al., 2016), psychotropic drugs are typically given to these patients to lessen the symptoms of the disorders, such as anti-anxiety medications and sleeping pills.

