### Experimental group treatment

The experimental group receive evidence-based group cognitive-behavioral treatment. The protocol that will be applied is based on the protocol originally designed by the PsicAP group in Spain, led by [name]. The protocol is based on 7 sessions, with each lasting 90 min. It will be offered once per week in groups of up to 8 people. The sessions are made up of the following elements:

Psychoeducation that focuses on providing guidance about what emotions actually are as well as their purpose, on the difference between normality and disorders surrounding emotions, and other useful information to counteract some of the misconceptions that the population tends to have about emotions and EDs.Relaxation techniques focused on reducing the physical sensations of discomfort that can trigger ED, including abdominal breathing and progressive muscle relaxation.Training in cognitive restructuring to ensure that patients can identify cognitive distortions and pathological or irrational thoughts that they experience in everyday situations so they can replace them with more logical and healthy alternatives, thus making a change to the emotional intensity associated with distortions and thinking errors.Behavioral therapy, so that patients can identify their emotions and any flawed strategies they may have for regulating emotions and dysfunctional behaviors, replacing them with more functional strategies and repeating them until the individuals develop healthier and more adaptive habits to replace the old patterns.Relapse prevention, to maintain long-term change and ensure that participants can identify their risk situations and the alternatives they have for dealing with them. This includes practicing problem analysis skills from a cognitive-emotional perspective, Use the tools and practical exercises that have helped us. Continuing to practice, until it is overcome. Receiving an additional psychological appointment.

Table 1 outlines the resources used for each component.

**Table 1 Tab1:** PsicAP Protocol components and resources

Therapeutic components	Resources
Psychoeducation	Information about emotions, anxiety, emotional disorders, cognitive-behavioral treatment components, cognitive errors, the relationship between thought and emotion, clarifications about existing misinformation surrounding emotions and emotional disorders.

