## Data analysis

Intention-to-treat (ITT) analysis will be performed. The ITT analysis will include all randomized patients in the groups to which they were randomly assigned. Analysis will take into account noncompliance, protocol deviations, dropouts, and anything else that happens after randomization. The two randomized groups will be compared in the treatment period; posttreatment; and at 3 and 6 months after treatment finalization. In addition, within-subject comparisons will be analyzed, contrasting pretreatment and posttreatment scores. The within-group and between-group differences will be examined using mixed-effect models, since these are considered more accurate than univariate and multivariate repeated measures of variance. Group differences will be analyzed after controlling for baseline levels, gender, age, and treatment center. Analysis will be carried out using SPSS version 21.0 (IBM Corp).

For primary outcomes, will consider group differences in anxiety (GAD-7), depression (PHQ-9), and somatic symptoms (PHQ-15) comparing baseline and post-treatment scores using a mixed-effect model. For secondary outcomes, will check between-group differences in the level of disability on daily life domains (work, social, and family life) and quality of life domains (physical, psychological, social, and environmental). The effect sizes of the treatment on primary and secondary outcomes (mean scores) will calculate by applying Morris’s d statistic, where the standardized effect of the treatment is defined as the difference between groups in mean PPC values, divided by the common standard deviation. In addition, a per-protocol (PP) analysis for primary and secondary outcomes will performer only in the patients who completed all follow-up measurements.

Finally, will calculate additional analyses: recovery, reliable recovery, and deterioration rates. The recovery index was defined as pre- treatment scores above the threshold on any of the three scales and below the threshold on all scales at either the post-treatment or 6-month follow-up assessment. The reliable recovery rate will calculate using a change score based on the standard deviation (S.D.). Thus, will use a change score of ≥5 for the GAD-7 and ≥6 for the PHQ-9 and the PHQ-15.

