## Results

The project’s recruitment phase began on August 9, 2021 and will remain open until the target sample is reached. All post-treatment evaluations are expected to be completed by May 2023.

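### Assessments are timed from session seven or the end of treatment, which usual care does not have, so the arms can be measured at different times since randomization

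*Protocol article*

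**What the plan says.** The article dates its assessments in several ways.

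- **Study design:** "Study participants will be assessed at 6 and 12 months after the seventh study session". This covers participants in both arms.
- **Data analysis:** "The two randomized groups will be compared in the treatment period; posttreatment; and at 3 and 6 months after treatment finalization".
- **Data collection:** the baseline battery is repeated when treatment is complete. The Treatment satisfaction survey is likewise placed at the end of treatment, for all participants.
- **Main objective:** effectiveness is evaluated "in the Dominican Republic at 3 months, and to explore if results are maintained over time (6 months"), with no starting point for either interval. Secondary objectives also names 3 months without an origin.

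The sessions belong to one arm. Experimental group treatment states: "The protocol is based on 7 sessions, with each lasting 90 min", held weekly in groups of at most eight. For the other arm, Control group treatment states: "The control group will receive the TAU provided by the primary care physician at the PC center". It adds that earlier research has described such care as "no treatment, standard treatment, pharmacological treatment and/or practical advice by the GP provided in routine care".

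**The concern.** A between-arm comparison of change is interpretable only if both arms are observed over the same interval. Here the stated origin is an event in the PsicAP arm with no counterpart in usual care, so someone must decide when each control is due, and the article does not say how.

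Patients enter because they exceed a symptom cut-off (Target population), so some improvement without PsicAP is to be expected. If one arm is measured later than the other, the extra elapsed time is mixed into the estimated effect on GAD-7, PHQ-9 and PHQ-15. The way therapy is delivered makes unequal timing possible: patients are randomized individually, while therapy is given in groups. A PsicAP patient may wait for a group to form, and that wait moves session seven. Nothing in the article moves a control's assessment to match.

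**Working it through.** The plan states no figure on this point, so there is none to reproduce. The check sets the sections side by side, followed by one illustration.

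**1. Does each anchor exist in each arm?**

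| Section | Anchor | PsicAP arm | Usual-care arm |
|---|---|---|---|
| Study design | seventh session | yes | no sessions |
| Data analysis | end of treatment | yes | no defined end; may be no treatment |
| Data collection | completion of treatment | yes | no defined completion |
| Main and Secondary objectives | none stated | – | – |

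No section times an assessment from randomization, ties controls to a therapy group's calendar, or says on what date a PsicAP patient who stops early is assessed. Limitations expects a high risk of incomplete attendance, and Data analysis keeps all randomized patients in the intention-to-treat comparison. Both groups of patients therefore need dates.

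**2. How far could session seven move? (illustration only)**

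Inputs from the article: 150 per arm (Patient recruitment); 6 centres (Study space); recruitment from 9 August 2021, with post-treatment evaluations expected to finish by May 2023 (Results); weekly sessions in groups of at most 8 (Experimental group treatment).

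Assumptions not in the article: even accrual across centres and over time, groups formed within a centre, and randomization before the wait.

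- Session 1 to session 7: 6 weeks = 42/30.44 = 1.4 months.
- Recruitment period: 9 August 2021 to 31 May 2023 = 21.7 months; less 1.4 = 20.3 months.
- PsicAP accrual per centre: r = (150/6)/20.3 = 25/20.3 = 1.23 per month.
- Wait of the first patient in a group of g: (g − 1)/r. Mean wait: (g − 1)/(2r).

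| Group size g | First patient waits (months) | Mean wait (months) |
|---|---|---|
| 2 | 0.8 | 0.4 |
| 4 | 2.4 | 1.2 |
| 6 | 4.1 | 2.0 |
| 8 | 5.7 | 2.8 |

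The last patient to join any group waits about 0 months and reaches session seven at about 1.4 months. The first patient in a group of 8 reaches it at 5.7 + 1.4 = 7.1 months. The control arm has no corresponding date to set against this range.

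**3. Can this be turned into a bias?**

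No. That would need four things the article does not give: actual waiting times, the minimum group size, whether baseline comes before or after the wait, and when controls are assessed. It would also need a rate of improvement under usual care.

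**The case against.** The strongest reply is that this is a journal article and that dating control visits is operational detail for the full protocol. The Study design rule is also compatible with assessing controls on the calendar date of a concurrent group's seventh session. Part of this stands: a full protocol may contain such a rule, and the article does not show that the arms will differ. But the article does not leave timing to another document. It states an origin for all participants, and that origin has no defined meaning for half of them. That is a rule badly fixed, not only a gap.

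Three stronger readings are tempting, and the article does not support them.

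- **A bias of known size.** Multiplying mean waits of 1.2 to 2.8 months by an assumed 0.05 to 0.10 SD of improvement per month gives 0.06 to 0.28 SD, which looks large beside the cited effects of 0.40 to 0.65. Every link is assumed. Data collection can be read as placing baseline at the start of treatment; the wait would then precede baseline and add nothing to the pre-post interval. Nothing says that controls are measured without a comparable delay. Selection above a cut-off also produces regression to the mean, which appears largely at the first re-measurement in both arms and not at a steady monthly rate.
- **Early leavers have no possible date, so data go missing in one arm only.** A group's seventh session has a calendar date whether or not a given patient attends. Data collection also allows remote completion and telephone reminders. What is missing is only a statement that this date applies.
- **Every time point is tied to the PsicAP sessions.** The objectives name months with no anchor at all.

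**Conclusion.** The point holds as a defect in the timing rule. The stated anchors exist only in the PsicAP arm, no matching date is given for controls, and the arms can therefore be measured at different times since randomization. Any wait for a group lengthens that time in the PsicAP arm only.

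Neither the size nor the direction of a bias follows from the article. The 1.4 to 7.1 month range shows that the anchor could move appreciably under the assumptions listed. It is not an estimate of what will happen and not a difference between arms. Preferring the end of treatment over session seven would not cure the problem, since usual care has neither.

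Separately, Study design gives follow-up at 6 and 12 months, while Main objective names 3 and 6 months and Data analysis says "at 3 and 6 months after treatment finalization". These cannot all be the schedule.

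The change should be made because it protects the primary between-arm comparison at modest cost.

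**What to change.** Define one time origin that applies in the same way to both arms. Either:

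1. time every assessment at a fixed interval from randomization; or
2. link each control at randomization to the concurrent therapy group at the same centre, and use that group's post-treatment and follow-up calendar dates.

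State that PsicAP patients who stop early are assessed on their group's scheduled session-seven and follow-up dates. Record the days from randomization to each assessment and report them by arm; this also shows how comparable the timing was for patients already assessed. In the same edit, reconcile the follow-up times across Study design, Main objective and Data analysis, and give the origin for each.

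**Cost.** No extra visits. Under option 1 the interval since session seven varies within the PsicAP arm, and if waits are long an early fixed date could fall before the sessions end, so the interval has to be chosen with the actual waits in view. Under option 2 control visits must be scheduled to a group calendar. Holding back randomization until a group is ready would also align the arms, but it changes the enrolment procedure of a trial that has been recruiting since August 2021 and is more than a change of wording.

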## Methods

### Study space

This is a multi-center trial carried out in 6 PHC centers; in most of these centers, psychological service is either non-existent or severely limited.

In order to improve mental health services in the country, the study protocol will initially be implemented in the following PHC centers in Santiago de los Caballeros, Dominican Republic: [name] Primary Health Center, El Guano Primary Health Center, Mamachen Primary Health Center, Barrio Obrero Community Center, Hato Mayor UNAP Center and Gurabo Diagnostic Center.

### Target population

The total intended sample that will be reached in this project is 300 Dominican adults aged 18 to 79. Adult patients from PHC centers who exhibit emotional symptoms (anxiety, depression or somatization) or probable mild to moderate anxiety (generalized or panic), mood or somatization disorders that have been assessed using the Patient Health Questionnaire (PHQ) are eligible (26–27) Specifically, those who meet the study inclusion criteria for the possible diagnosis of any of these disorders or have exceeded the cut-off score on any of the corresponding sub-scales will be part of the study: General Anxiety Disorder-7 (GAD-7) (generalized anxiety ≥ 10), PHQ-9 (depression ≥ 10), PHQ-15 (somatization ≥ 5), PHQ- Panic Disorder (PHQ-PD) (positive and panic ≥ 8, including the first 4 items). Patients who score ≥ 24 on the PHQ-9 or with suicidal ideation will be excluded and referred to a specialist.

All patients in PHC centers will have the same opportunity to be assessed in order to determine whether they could benefit from PsicAP psychological treatment. Those who meet the study inclusion criteria will be invited to be part of the study and, after accepting and signing the informed consent of their own free will, they will be distributed equally at random (1:1) between the control group (receiving the conventional treatment used in PHC facilities up to this point) and the experimental group (who will receive the PsicAP treatment).

## Inclusion and exclusion criteria

### Inclusion criteria

Be between the ages of 18 and 79.Have anxiety, depression with a PHQ-9 intensity level that is ≥ 10, but not exceeding 24 points.Have a positive result for somatization (3 or more symptoms at maximum intensity).Not be receiving psychological treatment/psychotherapy.Be Dominican.Be able to read and speak Spanish at a basic level (elementary education).

### Exclusion criteria

Have a diagnosis for a severe mental disorder such as bipolar disorder or a personality disorder.Have had a recent serious suicide attempt.Have a serious work, family or social disability.Have a severe emotional disorder (ex., comorbidities with substance abuse disorders) or other severe mood disorders.

## Interventions

### Control group treatment

The control group will receive the TAU provided by the primary care physician at the PC center. This treatment has been described in previous research as no treatment, standard treatment, pharmacological treatment and/or practical advice by the GP provided in routine care (Watts et al., 2015). In the Dominican Republic, as in other countries such as Spain (Cano-Vindel et al., 2016), psychotropic drugs are typically given to these patients to lessen the symptoms of the disorders, such as anti-anxiety medications and sleeping pills.

### Experimental group treatment

The experimental group receive evidence-based group cognitive-behavioral treatment. The protocol that will be applied is based on the protocol originally designed by the PsicAP group in Spain, led by [name]. The protocol is based on 7 sessions, with each lasting 90 min. It will be offered once per week in groups of up to 8 people. The sessions are made up of the following elements:

Psychoeducation that focuses on providing guidance about what emotions actually are as well as their purpose, on the difference between normality and disorders surrounding emotions, and other useful information to counteract some of the misconceptions that the population tends to have about emotions and EDs.Relaxation techniques focused on reducing the physical sensations of discomfort that can trigger ED, including abdominal breathing and progressive muscle relaxation.Training in cognitive restructuring to ensure that patients can identify cognitive distortions and pathological or irrational thoughts that they experience in everyday situations so they can replace them with more logical and healthy alternatives, thus making a change to the emotional intensity associated with distortions and thinking errors.Behavioral therapy, so that patients can identify their emotions and any flawed strategies they may have for regulating emotions and dysfunctional behaviors, replacing them with more functional strategies and repeating them until the individuals develop healthier and more adaptive habits to replace the old patterns.Relapse prevention, to maintain long-term change and ensure that participants can identify their risk situations and the alternatives they have for dealing with them. This includes practicing problem analysis skills from a cognitive-emotional perspective, Use the tools and practical exercises that have helped us. Continuing to practice, until it is overcome. Receiving an additional psychological appointment.

Table 1 outlines the resources used for each component.

**Table 1 Tab1:** PsicAP Protocol components and resources

Therapeutic components	Resources
Psychoeducation	Information about emotions, anxiety, emotional disorders, cognitive-behavioral treatment components, cognitive errors, the relationship between thought and emotion, clarifications about existing misinformation surrounding emotions and emotional disorders.
Relaxation techniques	Abdominal breathing exercises and audio, progressive muscle relaxation and changes in focus.
Cognitive restructuring training	Ellis ABC model, information about rational and irrational thoughts, and exercises to detect and analyze irrational thoughts and distinguish them from irrational [sic] ones, identify and restructure thinking errors and provide positive self-instructions.
Behavioral therapy	Behavioral activation, exposure therapy and techniques, and training in social skills, assertiveness and problem solving.
Relapse prevention	Problem analysis skills from a cognitive-emotional perspective, tools and practical exercises that have helped us, continuing to practice, until it is overcome.

## Therapist training

Each PsicAP group is led by a therapist who is also working together with a co-therapist. All of the therapists who are assisting the patients in the Dominican Republic PsicAP project originally graduated with a Bachelor’s degree in psychology, which requires approximately 4 years of university training. One of the basic requirements for taking on a therapist role was also to have a master’s degree in clinical psychology or a related area. Some of the therapists also have a Ph.D. in psychology. Co-therapists have a degree in psychology but have not yet completed a master’s program. The latter received specialized training so they could carry out the initial and final project assessments and assist the therapists appropriately during the sessions.

In order to standardize the therapeutic model to be followed, two significant types of training were done: (1) each therapist had to take an online course on the in TEA platform, which consisted of 45 h of training to refresh themselves on how to manage anxiety disorders (course name: “Refresher on the treatment of anxiety disorders: a cognitive-emotional and transdiagnostic approach” [*“Actualización en el tratamiento de los trastornos de ansiedad: un enfoque cognitivo-emocional y transdiagnóstico”*]); (2) therapists and co-therapists met once a week for seven weeks in order to share the slides and resources from each of the sessions that would be given to the participants, in an effort to establish guidelines so that the therapy in each of the centers would be as homogeneous as possible.

## Measures

### Generalized anxiety disorder test-7 (GAD-7)

The GAD-7 uses 7 items to evaluate how often people have been bothered by symptoms of generalized anxiety in the past two weeks. Each answer option is scored from 0 to 3, with the scale ranging from 0 to 21. Scores ≥ 5, ≥10, and ≥ 15 represent absent, mild, moderate and severe anxiety levels, respectively. According to various studies, the Spanish versions of both the GAD-7 and its short version (GAD-2) have appropriate reliability and validity levels for screening generalized anxiety disorder [28] and were validated in the Spanish PsicAP project [29].

